### Recruitment

Recruitment will vary across implementation countries to ensure a recruitment method that is adjusted to the specific study design of each country, sample characteristics, and country culture. Potential participants from the general population will receive an invitation to register in the study via newspaper, social media, internet, pastoral care, social care, or personal contacts from health care professionals. For each implementation country, an assessment of the recruitment strategy will be conducted 1 month after the start of the trial to decide whether the recruitment contingency plan will be implemented.

### Randomization

All eligible participants are randomly assigned to the active arm of the study (including the 2 active arms, standardized or self-tailored intervention format for the trial in Switzerland) or to the control or care-as-usual groups, depending on the implementation country. Participants assigned to the active arms will receive a participant code that gives them access to the self-help program and will be asked to use it for 10 weeks. Participants in the waitlist control group will start using the program 10 weeks after randomization. In Portugal, participants in the care-as-usual group can use the program after 20 weeks of follow-up, if requested.

For the 3 trials, the block-wise randomization was performed by an external programmer not involved in the trial using a random allocation sequence. The trials are unblinded. In Switzerland, the participants register on the study website and fill out the baseline questionnaire. Then, a member of the study team conducts the screening telephone call and allocates the participants to the 3 arms based on randomization numbers provided by the external programmer. In the Netherlands and in Portugal, participants are directly contacted by the teams responsible for implementing the study. Contacts are made based on their own professional lists. In the 3 countries, participants receive the intervention link after their eligibility has been confirmed in a phone call or an individual interview, depending on the implementation country.

### Description of the Intervention

#### Content

The content of the intervention was designed to follow the content structure of LIVIA [14,34]. However, unlike LIVIA, the content will be provided to participants through a conversational virtual agent, Sun, who guides the user through the *Study* section (the CBT intervention itself; Figure 1). During the onboarding and the completion of study modules, users will be invited to use the other sections of the intervention: Notebook, Activities, and My Support. The Notebook is where users can find their notes from the study modules and are provided with a shortcut for the most important exercises. The Activities section provides suggestions for activities that encourage mourners to try new daily tasks or routines aimed at promoting mental and physical well-being. Finally, in My Support, participants can find a reminder of the hotlines or people they can contact to ask for additional support, alongside a summary of their best strategies to find support, which corresponds to some of the exercises completed in the study modules.

**Figure 1 figure1:**
[figure not shown]
Screen of the web-based self-help program showing the first 6 modules and the available functionalities (right top corner).

The main section of the intervention is the *Study* section which comprises 10 modules that address topics intended to support either the acceptance of the loss or the restoration and adaptation to a new life. The modules are divided in several submodules, which correspond to specific subtopics or different types of exercises. The first 2 study modules include general information about (1) the impact of the loss of a partner and grief reactions and (2) an assessment of the current personal situation. Modules 3 to 5 focus on resources and restoration-oriented tasks for fostering positive thoughts and emotions as well as self-care. Modules 6 and 7 consist of loss-oriented interventions for accepting memories and pain and for addressing unfinished businesses, events that the mourner may see as unresolved. Modules 8 and 9 again include restoration-oriented tasks focusing on creating a new life without the partner and social relationships. The last module, module 10, addresses the redefinition of the relationship with the deceased person.

The modules and submodules include (1) readings—that is, texts based on scientific knowledge about grief-related topics that provide the background and rationale for the modules; and (2) exercises encouraging mourners to actively reflect on their lives, their grief, and what was learned in the readings, besides applying their new knowledge to their daily life and regularly practicing the new coping strategies and routines. Within the *Study* section, the conversational agent introduces the modules and submodules, guides users through them, wraps up the modules and submodules, and suggests the completion of the self-reflection items, where participants are asked to assess how helpful the completed submodule was.

The content is delivered in 2 formats, corresponding to the 2 active arms of the trial conducted in Switzerland. In the standardized intervention format, the presentation of the modules is based on a fixed order, in which the next modules are only accessible after the former was completed. In the self-tailored intervention, only modules 1 and 2, focusing on information about grief reactions and an assessment of the current personal situation, respectively, are mandatory and are required to be completed at the start. The remaining modules become available after the completion of module 2, and from then on, the participants can decide on which module they want to work on next.

The German content of LIVIA was translated and further developed in English by the clinical team of the project. Subsequently, all content was translated from English to German, Dutch, and Portuguese by the research teams of each country with expertise in adult health care. The translated content was implemented in the web-based platform and tested by primary end users (older mourners) in user-experience tests. On the basis of the test results, changes were made in the English version by the clinical team of the project, followed by the respective translations. This iterative process of content development, translation, and testing ensured that the content is consistent among the implementation countries and is adapted to each cultural language specificities, without losing its clinical validity.

#### Mood Self-check

Participants will be asked every other week to complete a set of questions to self-check their mood and perceived progress in the program. This will also enable the program to assess whether participants are experiencing intense psychological distress. In addition, based on users’ answers in this self-check questionnaire, participants can be suggested to seek further support if high and prolonged distress in the mood self-assessment is reported or if they do not perceive that any progress was made while using the self-help program.

#### Participants’ Guidance During the Trial

During the 10 weeks of the intervention, users will be able to receive guidance, which varies depending on the country-specific research goal, target population, and structure of the research team. In Switzerland, participants will receive via email a short weekly feedback and support from a trained coach, whereas users in Portugal will be contacted via telephone every other week on the grounds of technical support and troubleshooting. This guidance is intended to acknowledge and motivate participants for their work with the self-help program and to provide a weekly structure for the use of the program. Moreover, it will ensure the identification of potential technical problems and create the opportunity for participants to ask further questions. This guidance will also be based on participants’ self-reported mood and therapeutic progress within the program. In the Netherlands, where the complementary research goal is to assess technology acceptance, guidance will follow a passive format in which participants will be able to contact the intervention’s team via email or telephone in case they need further support.

### Measures

#### Overview and Measurement Times

All clinical outcomes are self-report measures and will be completed on the web or within the program. In the trials conducted in Switzerland and the Netherlands, for the active arms, measurements of primary and secondary outcomes will take place (1) before users start using the program at baseline; (2) after the intervention, 10 weeks after the start of the program; and (3) at follow-up, 20 weeks after the user starts the program, which will measure the stability of the outcomes over time. For the waitlist control groups, the measurement times will occur at baseline (week 0), after 10 weeks waiting to start the intervention, after completing the intervention (week 20), and at follow-up (week 30). In the trial conducted in Portugal, the active arm and control group, care as usual, will occur at baseline, 10 weeks after starting the intervention, and at follow-up, 20 weeks after starting the intervention.

As no cross-cultural comparisons are planned, measures will be adapted to each country’s trial. The measures used in the 3 different countries depend on the measures available for each language, which will result in the use of equivalent measures when it is not possible to use the same. Primary and secondary outcomes will allow for testing the efficacy.

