##### Perceived Loneliness

Perceived loneliness will be measured with the de Jong Gierveld Loneliness Scale [39,40] in Switzerland and the Netherlands. These will use the revised and shortened version of the scale with 6 items that resolve into social and emotional subscales [41]. In the Portuguese trial, perceived loneliness will be measured by the University of California, Los Angeles Loneliness Scale [42]. This scale has 18 items that measure subjective feelings of loneliness and social isolation.

In the trials conducted in Switzerland and in the Netherlands, primary and secondary outcomes will be determined after the intervention and after 10 weeks of using the intervention for the active arms and after 10 weeks of waiting to use the intervention for the control group. In Portugal, primary and secondary outcomes will be determined after 10 weeks of starting the trial, for both the active arm and the care-as-usual groups.

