### Ethics Approval and Trial Registration

All participants will give written informed consent. In the 3 countries, a short telephone call will be conducted to assess whether participants meet the eligibility criteria. In Portugal, participants will have their eligibility fully checked in person, at baseline, with the presentation of the informed consent, after which the initial evaluation will continue. In Switzerland and Netherlands, eligible participants will receive a link to complete the primary and secondary outcomes for the baseline measurement.

Medical ethics approval has been obtained by the Medical Ethical Committee of Northwestern and Central Switzerland (Business Administration System for Ethics Committees number 2021-02221) and the Ethical Committee of Unidade Local de Saúde do Baixo Alentejo (EDOC/2021/48762). For the study in the Netherlands, the Medical Ethical Committee Oost-Nederland ruled that the study was exempt from obtaining medical ethical permission, as the main topic of the intervention and study (mourning) is not a medical condition (file numbers 2021-13268 and NL79937.091.21). The Portuguese and Swiss trials were registered at ClinicalTrials.gov (NCT05156346 and NCT05280041, respectively).

This study will be conducted in line with the Declaration of Helsinki, and no participant will be randomized unless written informed consent is available for that participant. Participants can withdraw from the trial at any time and will be informed and assured of such right. This study follows the principles of data protection and management described in the European Union’s General Data Protection Regulation. The trials were classified as having no or low risk; therefore, no protective measures for adverse events were mandatory. In the case of adverse events, the responsible ethics committees will be informed. Data monitoring committees are not required by the ethics committees. The ethics committees have the right to perform an audit at any time.

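### In Switzerland and the Netherlands the week-10 comparison counts time from program start in the active arms but from randomization in the waitlist, so the text permits later measurement of the active arm

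*Protocol article*

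**What the plan says.** **Switzerland and the Netherlands, active arms.** Overview and Measurement Times places the outcome measures "after the intervention, 10 weeks after the start of the program; and (3) at follow-up, 20 weeks after the user starts the program".

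**Switzerland and the Netherlands, waitlist.** The same section lists the control visits "at baseline (week 0), after 10 weeks waiting to start the intervention, after completing the intervention (week 20), and at follow-up (week 30". The Randomization section fixes where the wait ends: "Participants in the waitlist control group will start using the program 10 weeks after randomization". The Perceived Loneliness section restates the contrast for primary and secondary outcomes: "after 10 weeks of using the intervention for the active arms and after 10 weeks of waiting to use the intervention for the control group".

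**Portugal.** Overview and Measurement Times says that measurement in the active arm and the control group, "care as usual, will occur at baseline, 10 weeks after starting the intervention", with follow-up at 20 weeks on the same count. Perceived Loneliness says: "In Portugal, primary and secondary outcomes will be determined after 10 weeks of starting the trial", and applies this to both groups.

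**Baseline.** For Switzerland, the Randomization section says that "the participants register on the study website and fill out the baseline questionnaire". The screening call comes next, made by a team member who also allocates. Ethics Approval and Trial Registration says: "In Switzerland and Netherlands, eligible participants will receive a link to complete the primary and secondary outcomes for the baseline measurement". There, eligibility is assessed by telephone.

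**Analysis set.** The Statistical Analyses section keeps participants who do not complete the two mandatory modules in the intention-to-treat analysis, because they were randomized.

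**The concern.** A randomized comparison is fair at a given time after randomization. If one arm's visit is tied to an event that follows randomization, here first use of the program, the arms can differ in elapsed time as well as in treatment. The lag from randomization to first use cannot be negative, so any error goes one way: the active arm is measured later. The control visit cannot be moved back to match, because the waitlist receives the program at week 10.

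Elapsed time matters for this outcome. The Background section says that for most people grief weakens within weeks or months of the loss, and the Participants section admits people from 1 month after it. Extra time in the active arm could therefore be read as treatment effect on the primary outcome.

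Two related problems follow. A randomized person who never opens the program has no week-10 date, yet stays in the intention-to-treat set. Dropout is defined partly by not returning the postintervention questionnaire, which presupposes a due date. In addition, these are unblinded trials with self-reported outcomes, so a baseline answered after allocation could be coloured by knowledge of the arm. The order of baseline and allocation should not be open to doubt.

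**Working it through.** The documents give no figure for the size of this effect, so there is nothing to reproduce. The check sets the time origins side by side and then shows what a lag would do.

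**1. Time origins**

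| Trial | Active arm | Control arm | Same origin? |
|---|---|---|---|
| Switzerland, Netherlands | Program start (Overview); weeks of use (Perceived Loneliness) | Weeks of waiting (both sections), ending 10 weeks after randomization (Randomization) | No |
| Portugal, Overview | Intervention start | Intervention start, which care as usual does not have during the 20 weeks | Yes, but undefined for controls |
| Portugal, Perceived Loneliness | Trial start | Trial start | Yes |

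**2. Calendar offset at week 10 (Switzerland, Netherlands)**

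Let L be the weeks from randomization to program start. The documents do not give L.

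- Active arm measured at 10 + L weeks from randomization; waitlist at 10.
- Offset = (10 + L) − 10 = L.
- For assumed L = 0, 1 or 2, the active arm is measured at week 10, 11 or 12 against week 10, which is 0%, 10% or 20% more elapsed time.

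**3. Possible bias**

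Assume a linear natural decline of r SD per 10 weeks, and a baseline answered at about randomization in both arms. Then bias = r × L / 10, in favour of the intervention. The documents give no value for r; the values below are assumptions.

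| L (weeks) | r = 0.1 | r = 0.3 | r = 0.8 |
|---|---|---|---|
| 0 | 0 | 0 | 0 |
| 1 | 0.01 | 0.03 | 0.08 |
| 2 | 0.02 | 0.06 | 0.16 |

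The Sample Size section expects an effect above 0.80 against control. Relative to 0.80, a 2-week lag contributes between 0.02/0.80 = 2.5% and 0.16/0.80 = 20%.

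**4. Where week 20 matters**

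In Switzerland and the Netherlands the waitlist has received the program by week 20, and the Statistical Analyses section tests stability with time alone. There is no controlled week-20 contrast to bias. In Portugal, care as usual has no access to the program until the 20-week follow-up is over, and the Cost-effectiveness Analysis section covers the follow-up period, so the week-20 origin does matter there.

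**5. Order of baseline (Switzerland)**

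- Randomization section: baseline, then call, then allocation by the caller.
- Ethics section: eligibility by telephone, then the baseline link.

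Both orders cannot be right. If the Ethics order applied and allocation were still made at the call, baseline could follow allocation. The Overview section does not exclude this: for the active arms it requires only that baseline come before program use.

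**The case against.** The strongest reply is that no lag is documented. Active participants receive their access code on assignment, and visits are labelled by common week numbers. If first use follows at once, L = 0 and the two origins coincide. This stands: a reader might infer that the arms are in fact measured at different times, and the text does not establish that.

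The magnitude rests wholly on assumed rates. The upper rate of 0.8 SD per 10 weeks equals the whole planned effect, and no upper limit on time since loss is set, so many participants may be past any steep decline. This stands too.

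A reader might also set the possible bias against the 0.30 planned for self-tailored versus standardized delivery. That would be wrong, because both are active arms counted from program start.

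Nor does Portugal have arm-specific origins. Each section uses one origin for both groups; the fault is that the two sections disagree and that one origin does not exist for care as usual.

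Baseline after allocation arises only by taking the baseline timing from one section and the allocation timing from another. The conflict is shown for Switzerland only, and by itself it does not shift timing between arms.

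Finally, questionnaire send-dates are detail that an article may leave to the full protocol. That would answer a missing rule. Here the rules are stated, and they differ by arm or between sections. The 10-week window for completing the mandatory modules does not supply a questionnaire date for someone who never starts.

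**Conclusion.** The point holds as a defect in stated rules, not as a demonstrated bias. In Switzerland and the Netherlands the primary week-10 contrast has a different time origin in each arm, and any start lag would favour the intervention. The size is unknown: zero without a lag and, for an assumed 2-week lag, 0.02 to 0.16 SD if grief declines naturally and linearly by an assumed 0.1 to 0.8 SD per 10 weeks. Even the top of that range is well below the planned 0.80 against control, but it is not negligible.

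Three further points stand: never-starters in the intention-to-treat set have no defined week 10; the two statements of the Portuguese time origin conflict; and the two statements of the Swiss baseline order conflict. The documents do not show that any baseline is answered after allocation. The change should be made, since it is cheap and removes the timing offset by construction.

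**What to change.** 1. Within each trial, make the date of randomization the single time origin for all arms. Send the week-10 questionnaire on a fixed date from it whether or not the program was started; in Portugal do the same for week 20. This also gives never-starters a due date.
2. Reword the Portuguese schedule in Overview and Measurement Times and in Perceived Loneliness so that both use that origin.
3. Reconcile the Randomization and Ethics sections so that baseline is completed and locked before allocation is released.
4. Keep time since program start as a descriptive variable only.

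The cost is wording plus questionnaire send-dates in REDCap or Qualtrics. The small downside is that late starters are assessed with less than 10 weeks of use.

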#### Primary Outcome: Grief Symptoms

In the 3 implementation countries, grief will be assessed with TRIG (eg, [37]). TRIG is a widely used measure to assess the severity of grief. A recent factor analysis identified 3 factors for emotional response, thoughts, and nonacceptance regarding a loss. TRIG assesses the severity of grief from 1=completely true to 5=completely false.

#### Secondary Outcomes

##### Depression Symptoms

In the 3 implementation countries, depression symptoms will be assessed by the Patient Health Questionnaire-9, a self-administered version of the Primary Care Evaluation of Mental Disorders diagnostic instrument for common mental disorders. The Patient Health Questionnaire-9 scores each of the 9 diagnostic criteria for major depression in the Diagnostic and Statistical Manual, Fourth Edition. For each item, the answer format is a scale from 0=not at all to 3=nearly every day [38].

##### Perceived Loneliness

Perceived loneliness will be measured with the de Jong Gierveld Loneliness Scale [39,40] in Switzerland and the Netherlands. These will use the revised and shortened version of the scale with 6 items that resolve into social and emotional subscales [41]. In the Portuguese trial, perceived loneliness will be measured by the University of California, Los Angeles Loneliness Scale [42]. This scale has 18 items that measure subjective feelings of loneliness and social isolation.

In the trials conducted in Switzerland and in the Netherlands, primary and secondary outcomes will be determined after the intervention and after 10 weeks of using the intervention for the active arms and after 10 weeks of waiting to use the intervention for the control group. In Portugal, primary and secondary outcomes will be determined after 10 weeks of starting the trial, for both the active arm and the care-as-usual groups.

#### Potential Mediators and Change Mechanisms

##### Working Alliance

In the Swiss trial, the working alliance will be measured by the Working Alliance Inventory (WAI) [43,44], which is a measure of the therapeutic alliance, a key variable that accounts for treatment outcomes and users’ satisfaction across interventions (eg, [45]). The items of the WAI adapted for guided internet interventions were derived from the WAI‐short revised [46] and adapted to internet intervention programs with therapist support [44,47,48]. The task and goals subscale will be the one used, as it measures agreement with tasks and goals of the program (therapy), which includes 12 items to be rated on a 5‐point scale, from 1=never to 5=always. The working alliance will be assessed at weeks 2, 5, 8, and 10 after starting the intervention.

